#### Criteria for discontinuing or modifying allocated intervention {11b}

Given that the procedures in this study are generally low risk, the likelihood of participants’ withdrawal or discontinuation is minimal. However, since the participants are older adults with chronic diseases, the chance of dropping out due to sudden health deterioration is still possible. The participants will be able to discontinue the intervention sessions at any point at their request.

#### Strategies to assess and improve adherence to interventions {11c}

The participants will receive phone reminders about the date and time of the health coaching session. They are encouraged to stay for the entire intervention.

#### Relevant concomitant care permitted or prohibited during the trial {11d}

Participants will be excluded if they have enrolled in a concurrent lifestyle intervention research study during this study. However, participants can receive concomitant treatment (e.g. usual care, psychotherapy and pharmacotherapy), which will be assessed at follow-up.

#### Provisions for post-trial care {30}

No provision for post-trial care will be made because the interventions have been found to be safe. After completing the study, participants will return to their usual care.

### Outcomes {12}

Table 1 displays the SPIRIT flow diagram for the schedule of enrolment, intervention and assessment. Specifications of measures and data collection are provided below.

**Table 1 Tab1:**
[figure not shown]
SPIRIT flow diagram of the schedule of enrollment, intervention and assessment of the study

^a^Demographic variables include age, sex, education and number of chronic diseases

#### Patient activation

The 13-item Chinese version of the short-form Patient Activation Measure (PAM-13) [57, 58] will be used to assess patient knowledge, skills and confidence in self-management for chronic conditions. Sample items include ‘I am confident that I can follow through on medical treatments I may need to do at home’ and ‘I am confident that I can figure out solutions when new problems arise with my health.’ Each item is rated on a four-point Likert scale (1 = *strongly disagree* to 4 = *strongly agree*). The item response total will be transformed into an activation score ranging from 0 to 100 using the scale developers’ established algorithm [58], with a higher score denoting a high level of patient activation. A research license to use this scale will be obtained from Insignia Health, University of Oregon.

### Secondary outcomes

#### Depressive symptoms

The depressive symptoms will be measured by the 4-item short form of the Geriatric Depression Scale (GDS-4) [60]. Each item is rated using a binary scale (0 = *no* and 1 = *yes*). A higher summative score indicates more depressive symptoms in the past week.

#### Body mass index

The participants’ weight will be measured on the scale in light clothing, without shoes, and with a precision of 0.1 kg. Height will be measured to the nearest 0.1 cm by using a stadiometer with the stretch stature method and then converted to metres. BMI will be calculated using the standard formula (weight in kg)/(height in metres)^2^.

#### Blood pressure

Participants will be asked to rest for at least 15 min before blood pressure measurements are taken. Systolic and diastolic blood pressure will be measured twice, at a 2-min interval, on the left arm in a sitting position using an Omron HEM-7130 model automatic digital blood pressure monitor (Omron Healthcare, Kyoto, Japan). Each participant will be seated upright with his or her left arm supported at heart level. The mean of the first and second systolic and diastolic measurements will be reported as the blood pressure values for individual patients if the difference is within 5 mmHg. If the readings differ by more than 5 mmHg, the measurements will be repeated.

#### Participant timeline {13}

The participants’ flow for the trial is outlined in Fig. 1. Baseline data, including demographics and chronic diseases, will be collected in the pre-screening assessment. Eligibility of interested participants will be assessed by research assistants. Eligible participants will be randomly assigned to either one of the two arms (intervention or comparison group) and will subsequently be asked to complete the baseline and 3-month follow-up assessments.

**Fig. 1 Fig1:**
[figure not shown]
Flow chart of the study design

#### Sample size {14}

The required sample size is estimated for one of the primary outcomes, i.e. patient activation. With reference to previous studies of patient activation interventions on chronic disease self-management [43, 61], the sample size is estimated on the basis of an effect size *f* = 0.2. Using G*Power, power analyses revealed that a total sample size of 266 is required to detect differences amongst the two intervention conditions (i.e. health coaching delivered by lay health workers vs. health professionals), using a multivariate analysis of variance with an effect size of 0.2, a power of 90% and an alpha level of 0.05, with 133 individuals in each condition. Considering the dropout rate of 30% over a period of three months, the target sample size is adjusted to 380 (with 190 individuals in each condition).

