This study will pay particular attention to the effects of lay health coaching on community-dwelling older adults with diverse chronic diseases. Previous health coaching studies were often conducted on relatively younger patients, with at least half of the participants being under 60 years [16, 40–42]. Whether health coaching is still effective in older adults, particularly those with low educational attainment, remains uncertain. Furthermore, health coaching studies have often focused on specific diseases such as diabetes and COPD [16, 41]. Consequently, the findings of these studies may not be generalisable to older adults with multimorbidity, which constitutes over 50% of the older population worldwide [3]. For example, by using trials within cohort design, Panagioti et al. [43] found that although older adults with multimorbidity participating in a 6-month telephone health coaching demonstrated lower levels of emergency care use, their patient activation, quality of life and risk of depression did not significantly improve compared with those with only usual care. To address these knowledge gaps, the present study adopts a randomised controlled trial (RCT) design to compare the effects of health coaching interventions delivered by lay health workers and health professionals in community-dwelling older adults with diverse chronic diseases.

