### Objectives {7}

This study aims to (1) examine the effects of health coaching in community-dwelling older adults with various chronic diseases, and (2) compare the effects of two types of health coaches (i.e. health professionals and lay health workers) on health coaching outcomes. The effectiveness of health coaching is often measured through individual changes in health knowledge and behaviours, psychological status and clinical outcomes [36, 44]. With reference to previous health coaching studies [40, 43, 45, 46], the present study will measure patient activation, physical activity and nutrition behaviours as primary outcomes and depressive symptoms, body mass index (BMI) and systolic and diastolic blood pressure as secondary outcomes. This study hypothesised that the primary and secondary outcomes will be improved after participation in health coaching, and the improvements in health coaching delivered by lay health workers are comparable to those delivered by health professionals.

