#### Intervention description {11a}

The comparison and intervention groups will be assigned to a health coaching intervention. The comparison group will receive a health coaching intervention delivered by health professionals, such as nurses and dieticians, to promote a healthy lifestyle and self-management of chronic diseases. The intervention group will receive the same health intervention, except that it is delivered by lay health workers, including health promotion workers and graduates in health studies. Thus, the procedure and format of health coaching interventions remain the same across comparison and intervention groups whilst the clinical knowledge and experience of health coaches vary between them.

The health coaching intervention implemented in this study is based on effective health coaching components (e.g. motivational interviewing techniques and solution-focused goal setting) identified in systematic reviews and studies of health coaching in chronic disease management [34, 43, 51, 52]. All health coaches must complete over 100 h of training in a health coaching curriculum [53], supplemented with chronic disease-specific content (e.g. symptoms and regimens). The curriculum covers active listening and non-judgmental communication, navigating healthcare systems, setting self-management goals and motivational interviewing techniques. Although older adults may have different chronic diseases, they face similar challenges in managing their health conditions [54]. The chronic disease-specific content thus covers guidance for medication adherence, physical activity, dietary modifications and health monitoring. Due to the pragmatic nature of the study, further supervision processes will not be possible. Similar to previous studies, the health coaching intervention proceeds for 3 months [55, 56], and health coaches provide one-on-one support to older adults with chronic diseases, with a maximum caseload of 20 older adults at any given time. There will be a minimum frequency defined as one in-person or telephone contact every 6 weeks.

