## Discussion

The increasing prevalence of chronic diseases in older adults poses significant challenges not only to individual well-being but also to the primary healthcare system. Effective self-management interventions to enhance older adults’ health knowledge and support changes in health behaviours are important for aging-in-place. This study protocol, therefore, describes the design of an RCT for the lay health coaching intervention. The focuses of the study are to examine whether the beneficial effects of health coaching can be extended to older adults with diverse chronic diseases in a community setting and whether lay health workers are as effective as health professionals in delivering health coaching intervention. To the best of the authors’ knowledge, this study is the first study to directly compare the treatment effects of health coaching delivered by lay health workers and health professionals.

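### Nothing in the protocol supports the 0.4 SD lay-versus-professional difference behind the sample size, so the 90% power gives no assurance against smaller losses

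*Protocol article*

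**What the plan says.** Sample size {14} sizes the trial on patient activation and introduces its assumed effect with the words "With reference to previous studies of patient activation interventions on chronic disease self-management [43, 61], the sample size is estimated on the basis of an"; the value it then gives is f = 0.2. The total of 266 participants is described as "required to detect differences amongst the two intervention conditions (i.e. health coaching delivered by lay health workers vs. health professionals". The method and settings are given as "using a multivariate analysis of variance with an effect size of 0.2, a power of 90% and an alpha level of 0.05". Allowing for 30% dropout raises the target to 380.

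Four other places bear on that input:

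- **Background and rationale {6a}** describes reference 43 as a six-month telephone coaching study in older adults with multimorbidity. Of its participants it says that "their patient activation, quality of life and risk of depression did not significantly improve compared with those with only usual care".
- **Discussion** states, to the best of the authors' knowledge, that "this study is the first study to directly compare the treatment effects of health coaching delivered by lay health workers and health professionals".
- **Intervention description {11a}** makes the comparator active: "The intervention group will receive the same health intervention, except that it is delivered by lay health workers".
- **Objectives {7}** hypothesises that "the improvements in health coaching delivered by lay health workers are comparable to those delivered by health professionals".

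**The concern.** An effect size drawn with reference to studies of activation interventions is used as the difference between two ways of staffing one intervention. These are different quantities. The first concerns what an activation programme achieves. The second concerns what changes when only the coach's background changes. The protocol gives no reason to expect 0.40 SD for the second, and its own hypothesis points to a difference near zero.

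The consequence lies in how the result will be read. The Abstract and Discussion would use a favourable finding to support bringing lay workers into primary care. If the test is non-significant, a reader who sees 90% power in the sample-size section may take the result as good evidence that lay coaching is no worse. That inference would be sound only for losses of about 0.40 SD or more. Against smaller losses, the stated power says little.

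**Working it through.** **Inputs, all from Sample size {14}:** f = 0.2; alpha 0.05 (sidedness not stated, but the F test is non-directional); power 90%; 266 completers, 133 per arm; dropout 30%; target 380.

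**Step 1. Reproduce the plan's figure.** For two equal groups d = 2f, so d = 2 × 0.2 = 0.40 SD. The two-group F test has 1 and N − 2 degrees of freedom and noncentrality λ = f²N = Nd²/4. At N = 266, λ = 0.04 × 266 = 10.64 and power is 90.1%. At N = 264 it is 89.9%, so 266 is the smallest even total that reaches 90%. For dropout, 266 / 0.70 = 380. Both published figures reproduce. The section names a multivariate analysis of variance, but of the variants tried only the plain two-group test gives 266.

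**Step 2. Check the support for 0.40 SD in this contrast.**

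| Possible support | What the protocol says |
|---|---|
| Reference 43 | Comparator was usual care; no significant gain in activation |
| Reference 61 | Effect and comparator not described |
| Any direct lay-versus-professional study | None known to the authors |
| Difference in what the arms receive | Same intervention, different type of coach |
| Expected result | Comparable improvements |

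No row supplies a between-arm difference of 0.40 SD. That reference 61 is not a lay-versus-professional study is inferred from the Discussion's claim to be first, as far as the authors know.

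**Step 3. Power at other differences.** The protocol gives no estimate for this contrast, so the differences below are assumptions shown as a range. N = 266, alpha 0.05, same test.

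| Assumed difference (SD) | λ = 266 × d² / 4 | Power |
|---|---|---|
| 0.40 | 10.64 | 90% |
| 0.345 | 7.92 | 80% |
| 0.30 | 5.99 | 68% |
| 0.20 | 2.66 | 37% |
| 0.10 | 0.67 | 13% |

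A true difference of 0.20 SD would be missed about 100 − 37 = 63% of the time.

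**Step 4. What a non-significant result would leave open.** With 133 per arm the standard error of the difference is √(2/133) = 0.123 SD, so the 95% interval is about ± 1.96 × 0.123 = 0.24 SD. An observed shortfall of 0.20 SD for lay coaching would be non-significant, with an interval from −0.04 to 0.44 SD. That interval still contains the 0.40 SD for which the trial was sized.

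**Step 5. Departures from this simple test.** Statistical methods {20a} imputes missing follow-up with baseline values. If 30% drop out equally in both arms and the SD is unchanged (assumptions), a difference of 0.40 SD among completers becomes 0.70 × 0.40 = 0.28 SD in the full analysis set. The covariate adjustment planned in the same section may raise power. The Step 3 figures therefore describe a simple test in completers, not the exact power of the planned models.

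**The case against.** The strongest reply is that power depends on the assumed difference, alpha and sample size, not on who the comparator is. The section states its effect size in the same sentence as its power, so the 90% is formally correct. **This stands.** A reader might infer that the 90% is wrong, or cannot apply to an active comparator. The documents do not support that. What is missing is a reason to think 0.40 SD is the relevant difference.

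A second reply is that f = 0.2 is never reported as the effect of coaching. The protocol says only that earlier studies were consulted, and reference 43 is described as showing no significant activation gain. **This also stands.** A reader might treat 0.40 SD as the whole benefit of coaching, and conclude that the trial could detect only near-complete loss of it. The protocol gives no such figure and has no uncoached arm to estimate one, so power can be stated by size of difference but not by share of benefit kept.

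Third, the deeper difficulty may be that a comparability hypothesis is sized as a difference test, with no margin in the section. That is related but separate. Simply substituting a smaller difference would not resolve it. The sourcing problem would remain even if a difference test were the right analysis, because that test also needs a difference relevant to this contrast.

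Finally, a fuller justification might exist in the full protocol, which is not shown. That cannot be excluded. However, the article does name its source, and its own text shows that reference 43 does not fit.

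**Conclusion.** The point holds as a fault in the justification of the effect size, not in the calculation. The trial is sized for a 0.40 SD difference between two active arms. The one cited study that the protocol describes had a different comparator and no significant effect on the sizing outcome. The authors know of no earlier direct comparison, and the arms are expected to perform alike.

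The 90% is correct at 0.40 SD. It falls to 68%, 37% and 13% at 0.30, 0.20 and 0.10 SD. These figures assume 266 completers, equal arms, alpha 0.05 and an unadjusted two-group test. Which of these differences is realistic is unknown. The conclusion also relies on inference for reference 61, whose design the protocol does not describe.

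**What to change.** Leave enrolment as it is and make three changes.

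1. In Sample size {14}, stop presenting references 43 and 61 as the basis for the lay-versus-professional difference, and state that no estimate exists for this contrast.
2. Give power by assumed difference: with 266 completers in a simple two-group test, 90% for 0.40 SD, 80% for 0.345 SD, 68% for 0.30 SD, 37% for 0.20 SD and 13% for 0.10 SD. Add that baseline-value imputation of dropouts shrinks the difference and that covariate adjustment may raise power.
3. Commit to reporting the confidence interval for the arm difference. State that a non-significant difference will not be read as showing lay coaching to be as effective as professional coaching, and limit the conclusion to the size of difference the interval excludes.

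This needs no extra participants or procedures. The cost is wording in the sample-size and reporting sections, a less favourable power statement and a more restrained conclusion. Because Trial status expected recruitment to end in December 2024, a remedy that does not touch enrolment is the practical one.

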#### Recruitment {15}

The study protocol was approved by the Human Subjects Ethics Sub-committee of City University of Hong Kong. Older Chinese adults with chronic diseases will be invited through the centres of collaborating non-governmental organisations in different Hong Kong clusters. The study team will answer any questions raised and will ask for written informed consent if the older adult is eligible.

### Assignment of interventions: allocation

#### Sequence generation {16a}

Eligible participants will be randomised to either intervention or comparison groups on a 1:1 allocation ratio by using the R package *randomizr* [62] for R software (version 4.3.3). Four stratification factors, each with two levels, will be used: age (< 75 years vs. ≥ 75 years), sex, education (primary and below vs. secondary and above) and number of chronic diseases (≤ 2 vs. > 2). This stratification helps to reduce between-group differences at baseline and increase statistical power with a fixed sample size [63].

#### Concealment mechanism {16b}

Participants are randomised by an independent researcher by using R software, following a password-protected list with the allocation results. The allocation results will only be accessed by authorized study staff and the study coordinator upon randomisation by the independent researcher. The research assistants conducting baseline and follow-up assessments will not be informed about the allocation results.

#### Implementation {16c}

After obtaining written informed consent and collecting baseline data, an independent researcher will generate the allocation and inform the study coordinator about the results. To keep the research assistants blind to the allocation, the study coordinator will directly inform the health coaches about the list of assigned participants.

### Assignment of interventions: blinding

#### Who will be blinded {17a}

Research assistants, participants and health coaches are kept blind to the treatment allocation. The study coordinator will not be blinded but is strongly instructed not to disclose the assigned treatment during the study period.

#### Procedure for unblinding if needed {17b}

Not applicable. There is no need to unblind the research assistants, participants or health coaches.

### Data collection and management

#### Plan for assessment and collection of outcomes {18a}

Baseline and 3-month follow-up assessments will be conducted by trained research assistants to assess the primary and secondary outcomes. A detailed description of the instruments used in the study can be found in the ‘Outcomes {12}’ section. Data will be collected through the online survey platform QuestionPro to minimise data entry errors. All data will be anonymised and saved in a password-protected database on a firewall-protected local network server at City University of Hong Kong. Access to all data will be restricted to authorised study staff. The data will be stored, coded and cleaned in R software before analyses (e.g. checking for duplicates, coding of missing data and date of entry).

#### Plan for promote participant retention and complete follow-up {18b}

The health coaching sessions will be arranged between health coaches and participants upon mutual agreement. The participants will receive reminders from the health coaches regarding the day and time of the health coaching session. To maximise retention, the health coaching sessions will be conducted in participants’ homes or via telephone. Research assistants will follow-up with and motivate the participants for the 3-month follow-up assessment.

#### Data management {19}

Each participant will be assigned a unique participant identification code. All participants’ personal data will be encrypted with the identification codes. Demographic information linking the participants to the data will be stored in a separate file. All data will be entered into a password-protected database and managed on a firewall-protected local network server at City University of Hong Kong. Access to all data will be restricted to authorised study staff.

#### Confidentiality {27}

Identifiable individual participant information obtained in this study is confidential, and disclosure to non-relevant third parties is prohibited. The final dataset will contain only re-identifiable information (i.e. a unique participant identification code) and anonymised data entries. All publications associated with the results of the study will involve de-identified data, ensuring the confidentiality of participants.

